## Data management and monitoring

Each participant will be assigned a unique study identification (ID) number and identifying information will be placed in locked cupboards separate to other study data that will only be accessible to the authorized researchers. Paper copies of assessment tools will all be stored in locked filing cabinets in PILL premises. All anonymized data will be stored in encrypted and password protected computers. We will convene an independently chaired trial steering committee (TSC) to approve and provide oversight of the trial throughout its various stages. The TSC will include the PI, patient representative, Co-Is, an independent statistician, and an independent chair. The Data Safety and Monitoring Committee (DSMC) will monitor data and advise the TSC on

whether there are any ethical or safety reasons for why the trial should not continue. Both committees will meet twice in the first year and then once a year thereafter.

## **Discussion**

Empirical evidence from several trials lends support to patients gaining favorable outcomes when assigned to MBC compared to standard-care treatments (Zhu et al., 2021). This stepwise treatment, not only helps clinicians understand the patterns which lead to improvement, but also accelerates the process of sifting through various regimens to reach an effective treatment plan for the patient (Zhu et al., 2021). This is especially important for patients from low resource settings, who are already walking on the tightrope of low access and inconsistent resources in mental health. Hence, this trial aims to inform the feasibility and efficacy of implementing MBC in everyday clinical practice for patients with MDD in Pakistan.

## **Declarations**

### **Abbreviations**

MDD: Major Depressive Disorder; GBD: Global Burden of Diseases, Injuries, and Risk Factors Study; MBC: Measurement-based Care; STAR\*D: Sequenced Treatment Alternatives to Relieve Depression; SCID 5: Structured Clinical Interview for DSM-5; QIDS-RS: Quick Inventory of Depressive Symptomatology–Self-Report (QIDS-SR); (FIBSER): Frequency, Intensity, and Burden of Side Effects Rating scale; HDRS: Hamilton Depression Rating Scale; YMRS: Young Mania Rating Scale; TSC: Trial Steering Committee; DSMC: Data Safety and Monitoring Committee; (NBC) National Bioethics Committee ICH-GCP)International Conference on Harmonization Good Clinical Practice; GCP: Good Clinical Practices

### **Acknowledgements**

Not applicable.

**Funding**

Funding agencies had no role in the design and conduct of the study. The research team had full autonomy in all aspects of the study.

**Availability of data and materials**

Not applicable.

**Ethics approval and consent to participate**

Participants will be recruited at five local sites in Pakistan. The study has been approved by the National Bioethics Committee of Pakistan. All participants will provide written informed consent using a form approved by the local REB and will be advised of their right to withdraw from the study.

**Consent for publication**

Not applicable.

**Competing interests**

The authors declare that they have no competing interests.

## **Contents**

### **1. Specific Aims and Hypotheses**

### **2. Outcomes**

### **3. Statistical Methods**

#### **3.1. Interim Analyses**

#### **3.2. Statistical Analyses**

### **1. Specific Aims and Hypotheses**

The aim of this trial is to determine the efficacy and safety of MBC in patients with MDD in comparison with standard care in Pakistan. To reduce the variance found in treatment-as-usual and isolate the impact of MBC, this trial will limit medication choices to either paroxetine or mirtazapine (as per previously published trials). We hypothesize that, compared to standard care group, the MBC group will have significantly higher rates and shorter times to response and remission, along with lower rates of dropout and side effect burden.

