### ***Measurement-based Care***

At every outpatient visit, patient’s feedback will be recorded through the 16-item Quick Inventory of Depressive Symptomatology–Self-Report (QIDS-SR) (Rush et al., 2003) and the Frequency, Intensity, and Burden of Side Effects Rating scale (FIBSER) (Wisniewski et al., 2006). The QIDS-SR is used to measure depressive symptoms in the past one week, with higher scores indicating higher severity (Rush et al., 2003). FIBSER is completed by the patient to report antidepressant side effects on the domains of frequency, intensity, and burden (Wisniewski et al., 2006). A total score >4 is indicative of current treatment being unsuitable and requires revision to dosage/medication (Trivedi, 2009).

The patient’s responses on these self-report measures will inform and guide physician’s decisions. Following a stepwise approach, the treatment schedule will outline the dosage adjustment, and medication changes needed to mitigate the side effects, and promote therapeutic benefit for each patient. Originally driven from the STAR\*D project ([www.star-d.org](http://www.star-d.org)), the treatment schedule used by the Guo et. al. (2015) study (Guo et al., 2015) will facilitate the treatment schedule (Table 1), for this study. However, the starting dosage has been modified following a discussion with the stakeholders, which highlighted patient preference for slower dose titration when initiating preference. Treating physicians will undergo a two-day training to get acquainted with use of MBC schedule. Moreover, an independent research coordinator will be designated at each site to compare the physician’s clinical notes against the MBC treatment guidelines to ensure compliance and standardization. In case of any deviation from the MBC schedule, the physician will be notified and asked to make necessary treatment amendments.

*Table 1. The Measurement-Based Care Schedule*

| Time Point and Measure  | Clinical Status  | Treatment Plan                                                         |                                                                       |
|-------------------------|------------------|------------------------------------------------------------------------|-----------------------------------------------------------------------|
|                         |                  | Paroxetine                                                             | Mirtazapine                                                           |

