### **2. Outcomes**

A form will be designed to collect sociodemographic and clinical characteristics from the medical records, and this information will be confirmed in a clinical interview. HDRS scores will be used to inform two primary outcomes measures: estimated time from randomization to response (defining response as  $\geq 50\%$  reduction in HDRS from baseline) and remission (defined as HDRS score  $\leq 7$ ) (Hamilton, 1960).

Secondary outcome measures will include changes in severity of depressive symptoms (HDRS score). An additional checklist with six common side effects (dry mouth, diarrhea or constipation, dizziness or drowsiness, loss of appetite or nausea, headache, and excessive sweating); and the FISBER, will be used to measure side effects at each treatment visit. The pill count method will be used to measure treatment adherence.

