### 3.2. Statistical Analyses

A treatment-blind statistician will analyze the data after completion of follow-ups for all recruited participants using SPSS for Windows, version 20.0 (IBMCorp., Armonk, N.Y.).

Like the Guo et al. (2015) trial, we will use independent-sample t-tests, Mann-Whitney U tests, and chi-square tests, to compare sociodemographic and clinical characteristics, discontinuation, response and remission rates, and side effects as appropriate. Full intent-to-treat analyses will be carried out to determine all-cause discontinuation. Estimated time from randomization to response and remission will be calculated using Kaplan-Meier survival analyses, and a comparative analysis will be facilitated using the Cox proportional hazards regression model. Analysis of covariance will be used to compare the changes in HDRS scores between the two groups. Additional subgroup analysis might be carried out to understand group-differences due to age, gender, duration of illness, and number of previous episodes. The significance threshold will be  $p < 0.05$  (two-tailed) for all analyses.

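### The SAP hypothesises lower side-effect burden but names no measure that decides it, so several measures can each be tried at p < 0.05

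*Combined protocol and SAP*

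**What the plan says.** SAP section 1 gives the aim as efficacy and safety. Its hypothesis sentence, repeated in the protocol's Methods, ends with "along with lower rates of dropout and side effect burden". These are therefore stated hypotheses and go beyond routine safety monitoring.

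SAP section 2 separates two HDRS-based primary outcomes from the secondaries. For side effects it lists "An additional checklist with six common side effects" together with the FIBSER, both collected at each treatment visit. The protocol's Measurement-based Care section says that patients use the FIBSER to "report antidepressant side effects on the domains of frequency, intensity, and burden", and it also refers to a total score. For adherence, section 2 says: "The pill count method will be used to measure treatment adherence". Dropout is not listed as an outcome there.

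SAP section 3.2 uses t-tests, Mann-Whitney tests and chi-square tests to compare groups on "discontinuation, response and remission rates, and side effects as appropriate", and adds an intention-to-treat analysis of all-cause discontinuation. One threshold, p < 0.05, is described as "two-tailed) for all analyses". Neither document names a deciding side-effect measure or visit, defines a checklist total, or says which secondary results are exploratory.

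**The concern.** The side-effect hypothesis can be tested in several ways, and the plan does not choose among them before the data are seen. The six symptoms, a FIBSER total or the FIBSER domains could each be compared at the full 5% level, at any of several visits. A report that MBC is better tolerated could then rest on whichever comparison happened to reach significance.

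Safety is half of the stated aim, so such a claim would carry weight. The problem would remain even if the two primary outcomes were fully controlled for multiplicity, because nothing done for the primaries restricts the side-effect comparisons.

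**Working it through.** **Inputs**
- Per-test threshold: 0.05 two-sided (SAP 3.2), so 0.025 in the direction favouring MBC. This is the only error rate in the documents; no familywise rate is stated.
- Checklist: 6 symptoms (SAP 2).
- FIBSER: 1 test if a total is used, 3 if the domains are tested separately (protocol, Measurement-based Care). The SAP does not say which.
- Number of side-effect measures if tested singly: 6 + 1 = 7, or 6 + 3 = 9.
- Correlation between the tests, ρ: not given in the documents. Assumed range 0 to 0.8, equal for all pairs.

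**Formulas**, for k tests with no true difference
- Independent tests, either direction: 1 − 0.95^k. Favouring MBC: 1 − 0.975^k.
- Equal correlation ρ, with Φ and φ the standard normal distribution function and density:
  - either direction: 1 − ∫ [Φ((1.96 − √ρ·x)/√(1−ρ)) − Φ((−1.96 − √ρ·x)/√(1−ρ))]^k φ(x) dx
  - favouring MBC: 1 − ∫ [Φ((1.96 − √ρ·x)/√(1−ρ))]^k φ(x) dx

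**Check against the plan's own figure.** With k = 1 the formulas return 5% and 2.5%, which is the threshold in SAP 3.2.

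**Independent tests**
- k = 7: 1 − 0.95^7 = 30.2%; favouring MBC, 1 − 0.975^7 = 16.2%.
- k = 9: 1 − 0.95^9 = 37.0%; favouring MBC, 1 − 0.975^9 = 20.4%.

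**Across the assumed correlation, by numerical integration**

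| Measures (k) | Direction | ρ = 0 | ρ = 0.5 | ρ = 0.8 |
|---|---|---|---|---|
| 7 | either | 30% | 23% | 15% |
| 7 | favouring MBC | 16% | 11% | 7% |
| 9 | either | 37% | 27% | 17% |
| 9 | favouring MBC | 20% | 13% | 8% |

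The hypothesis is directional, so the rows favouring MBC are the ones that match the harm. They run from 7.4/2.5 = 3 times to 20.4/2.5 = 8 times the nominal rate.

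**Visits.** The table counts each measure once. The protocol's Assessment Procedure has five post-baseline assessments (weeks 2, 4, 8, 12 and 24), and the SAP collects side effects at each treatment visit. Testing at more than one of these would raise every figure.

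**The most restrained reading.** If side effects were compared only through one checklist summary and one FIBSER total, k = 2. With independent tests the chances are 1 − 0.95² = 9.75% in either direction and 1 − 0.975² = 4.9% favouring MBC. The SAP defines no such checklist summary.

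**The case against.** The strongest reply is that the SAP never commits to testing each item. It says only that side effects will be compared as appropriate. The protocol's reference to a FIBSER total points towards a single score, the checklist is described as additional, and the FIBSER has a burden domain that matches the hypothesis wording. This stands as far as the count goes: 7 to 9 is one reading. It does not remove the point, because the open choice of measure is itself the weakness.

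Second, the protocol's Sample size section calls the trial exploratory. That is correct, but the word describes the whole trial and appears once. The SAP does not repeat it, hypothesises significant differences, and applies a significance threshold throughout.

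Three stronger readings are tempting and should be resisted.
- A reader might infer that the secondary outcomes amount to 10 to 12 tests with about a 30% chance of a false finding. The documents fix neither number. Reaching 10 to 12 means testing every item singly and adding HDRS change, discontinuation and pill count, for which SAP 3.2 names no test. That count gives 40% to 46% if the tests are independent. About 30% needs an assumed correlation near 0.5, and it includes results against MBC.
- A reader might infer that the SAP accepts one significant symptom as proof of lower burden. It does not say so; it merely does not rule it out.
- A reader might infer that tolerability should be tested only after the efficacy results succeed. Nothing in the documents requires this. Safety is an aim in its own right, and the protocol's Introduction reports higher antidepressant doses under MBC in the trial being replicated. A side-effect excess under MBC should not depend on efficacy to be tested.

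**Conclusion.** The concern holds for the side-effect hypothesis. The SAP states it, provides several measures for it, gives each the full two-sided 5% level, and does not say which decides. If the items are tested singly, the chance of at least one false significant result is 15% to 37%, and of one favouring MBC 7% to 20% against 2.5%. These figures rest on 7 to 9 measures, one time point, no true difference, and an assumed common correlation of 0.8 to 0. Fewer summaries would lower them and repeated visits would raise them.

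The dropout hypothesis has a milder form of the gap: all-cause discontinuation is tested, but it is not listed as an outcome or named as the deciding test.

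This does not affect the validity of the primary analyses. It should be corrected because it leaves a tolerability claim open to chance and to selection after the results are known.

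**What to change.** In SAP sections 2 and 3.2, dated before unblinding:
- Name one FIBSER measure at one time point, for example the burden item at the final visit, as the sole test of the side-effect hypothesis. The protocol removes patients for intolerable side effects that cannot be managed, so also state how patients without that rating are handled.
- List all-cause discontinuation as an outcome and name it as the sole test of the dropout hypothesis.
- Report the six symptoms, the other FIBSER domains and pill count as exploratory, with group differences and 95% confidence intervals and no significance claim.
- Limit the p < 0.05 threshold to the primaries and the named tests. HDRS change and the response and remission rates then need an explicit status, as named tests or as exploratory.

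Each of the two hypotheses then has a single test, with a 2.5% chance of a false result favouring MBC.

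SAP section 3.1 describes the interim analyses in the past tense, so timing matters. If unblinding has already occurred, report all secondaries as exploratory with 95% confidence intervals.

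The cost is SAP wording only, since every measure is already collected. The downside is that a difference in a single symptom can no longer support a significance claim.

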### **2. Outcomes**

A form will be designed to collect sociodemographic and clinical characteristics from the medical records, and this information will be confirmed in a clinical interview. HDRS scores will be used to inform two primary outcomes measures: estimated time from randomization to response (defining response as  $\geq 50\%$  reduction in HDRS from baseline) and remission (defined as HDRS score  $\leq 7$ ) (Hamilton, 1960).

Secondary outcome measures will include changes in severity of depressive symptoms (HDRS score). An additional checklist with six common side effects (dry mouth, diarrhea or constipation, dizziness or drowsiness, loss of appetite or nausea, headache, and excessive sweating); and the FISBER, will be used to measure side effects at each treatment visit. The pill count method will be used to measure treatment adherence.

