## **Outcome measures**

A form will be designed to collect sociodemographic and clinical characteristics from the medical records, and this information will be confirmed in a clinical interview. HDRS scores will be used to inform two primary outcomes measures: estimated time from randomization to response ( $\geq 50\%$  reduction from baseline) and remission (HDRS score  $\leq 7$ ) (Hamilton, 1960).

Secondary outcome measures will include: severity of depressive symptoms (HDRS score), severity of manic or hypomanic symptoms according to the (YMRS score) (Young et al., 1978). An additional checklist with six common side effects (dry mouth, diarrhea or constipation, dizziness or drowsiness, loss of appetite or nausea, headache, and excessive sweating), along with FISBER, will be used to measure side effects at each treatment visit. The pill count method will be used to measure treatment adherence.

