## **Assessment Procedure**

This trial will include two experienced treatment-blind assessors at each site, who will independently administer the mentioned outcome measures at baseline and at 2, 4, 8, 12, and 24 weeks. The research coordinator at each site will advise and remind patients at each visit about non-disclosure of their treatment groups to the assessor.

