## Statistical analysis

We will analyze the data using SPSS for Windows, version 20.0 (IBM Corp., Armonk, N.Y.). Similar to the Guo et al. (2015) trial, we will use independent-sample t-tests, Mann-Whitney U tests, and chi-square tests, to compare sociodemographic and clinical characteristics, discontinuation, response and remission rates, and side effects as appropriate. Full intent-to-treat analyses will be carried out to determine all-cause and specific-cause discontinuation. Estimated time from randomization to response and remission will be calculated using Kaplan-Meier survival analyses, and a comparative analysis will be facilitated using the Cox proportional hazards regression model. Analysis of covariance will be used to compare the changes in HDRS and YMRS scores between the two groups. Additional sub-group analysis might be carried out to understand group-differences due to age, gender, duration of illness, and number of previous episodes. The significance threshold will be  $p < 0.05$  (two-tailed) for all analyses. A treatment-blind statistician will carry out interim quality checks and efficacy analysis, while final evaluation will be carried out after completion of followups for all recruited participants.

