### **3. Statistical Methods**

### 3.1. Interim Analyses

The protocol stated that a treatment-blind statistician may carry out interim quality checks and efficacy analysis. No interim analyses were needed, and none were done.

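### The SAP leaves out, without a reason, two analyses the protocol pre-specified: YMRS as a secondary outcome and discontinuation by specific cause

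*Combined protocol and SAP*

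**What the plan says.** **Protocol.** Under Outcome measures, the secondary outcomes include "severity of manic or hypomanic symptoms according to the (YMRS score"). Under Statistical analysis, the protocol states "Analysis of covariance will be used to compare the changes in HDRS and YMRS scores between the two groups" and "Full intent-to-treat analyses will be carried out to determine all-cause and specific-cause discontinuation". Under Assessment Procedure, blind assessors will "independently administer the mentioned outcome measures at baseline and at 2, 4, 8, 12, and 24 weeks".

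**SAP.** Section 2 states "Secondary outcome measures will include changes in severity of depressive symptoms (HDRS score"), then goes on to the six-item side-effect checklist, FIBSER and pill counts. Section 3.2 states "Analysis of covariance will be used to compare the changes in HDRS scores between the two groups" and "Full intent-to-treat analyses will be carried out to determine all-cause discontinuation". Section 3.1 says of interim analyses: "No interim analyses were needed, and none were done".

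Section 1 of the SAP keeps the protocol's aim of determining both efficacy and safety. It also keeps the hypothesis that dropout and side-effect burden will be lower under MBC.

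**The concern.** A SAP normally adds detail to the protocol's analyses. This one reduces them in two places that bear on safety, and says nothing about doing so.

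Both arms receive antidepressants. The protocol's Introduction reports that in the replicated trial the MBC arm had more treatment adjustments (44 against 23) and higher doses from week 2 to week 24. A scale for manic or hypomanic symptoms, and the reasons why patients stopped, are therefore relevant to a comparison of a more actively adjusted strategy with usual care.

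If the SAP is followed as written, neither analysis will be produced, while the report can still claim to have assessed safety. A later reader who compares the two documents will ask why the analyses went, and will find no answer.

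**Working it through.** No arithmetic bears on this point: it depends on no sample size, power or event figure. The check is a comparison of the two texts.

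| Item | Protocol | SAP |
|---|---|---|
| YMRS as secondary outcome | Listed (Outcome measures) | Absent (section 2) |
| ANCOVA of change | HDRS and YMRS (Statistical analysis) | HDRS only (section 3.2) |
| Discontinuation, intent-to-treat | All-cause and specific-cause | All-cause only (section 3.2) |
| Side-effect checklist and FIBSER | Included | Kept (section 2) |
| Between-arm tests of discontinuation and side effects | Included | Kept (section 3.2) |
| Efficacy and safety aim | Stated (Methods) | Kept (section 1) |

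**Step 1: are the omissions real?** Yes. The YMRS is missing from both SAP places where the parallel protocol sentence has it, and the reference to specific causes is missing from the one place where it would stand. The surrounding sentences are otherwise close to the protocol's.

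**Step 2: is a reason given?** No. SAP sections 1 to 3.2 explain neither change. Section 3.1 does comment on another departure from the protocol, the interim analysis, so the authors had a place to record such things.

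**Step 3: when was the SAP written?** The past tense of section 3.1 suggests that the interim question was already closed. That is as far as the inference goes. The protocol sets no date or information fraction for an interim look, and the SAP text available here carries no date. Section 3.2 still places the analysis in the future and gives it to a treatment-blind statistician.

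**Step 4: what is lost?**

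- *YMRS.* It is the only instrument in the plan described as measuring manic or hypomanic symptoms. The six checklist items are physical or general side effects, and FIBSER rates the frequency, intensity and burden of side effects. Neither replaces it.
- *Cause of discontinuation.* The protocol's Ethical and safety considerations name four grounds for removal: suicide attempt, pregnancy, severe medical condition, and intolerable side effects that could not be managed. Patients may also withdraw for any reason. Write D for the proportion discontinuing in an arm, S for the part due to the four named grounds and W for all other withdrawal, each patient counted once. Then D = S + W, and the between-arm difference in D is the difference in S plus the difference in W. A zero or favourable difference in D therefore does not fix the sign of the difference in S. An excess of intolerance stops in one arm may be hidden.

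**Step 5: would the data exist?** On its plain reading, Assessment Procedure covers the YMRS at baseline and at five follow-up visits. Since specific-cause discontinuation was planned, reasons should have been recorded too.

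**The case against.** The best defence is that silence is not withdrawal. The SAP is very short and never says that it replaces the protocol's outcome list. It also omits the stratification factors, the sample size and the assessment schedule, and nobody would treat those as cancelled. The protocol's plan may simply still stand. This has force as to intent, which the documents do not settle. It does not remove the problem: the analyst works from the SAP, and here the very sentences that carried these analyses were repeated without them. At the least, the two texts must be reconciled.

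The defence is also right about the following stronger readings, none of which the documents support:

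- *Selective reporting.* A reader might infer that the analyses went because of what the data showed. Nothing shows that anyone had seen YMRS or discontinuation results by arm.
- *No analysis of harm remains.* The checklist and FIBSER comparisons remain, and both parts of the stated hypothesis, dropout and side-effect burden, are still analysed. Neither document states a hypothesis about mania, and diagnosed bipolar disorder is an exclusion.
- *The YMRS is the only blind-rated safety scale.* The documents do not say who completes the side-effect checklist, and Assessment Procedure can be read to include it.
- *Intolerance stops rise while inefficacy stops fall under MBC.* No figure supports this. Under MBC, side-effect scores also prompt revision of treatment, so intolerance stops could fall. Inefficacy is handled by a switch within the trial and is not a listed ground for removal.

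**Conclusion.** The point holds as an unexplained reduction in pre-specified analyses. One secondary outcome with its ANCOVA, and one breakdown of discontinuation, are in the protocol and not in the SAP. The primary outcomes are untouched, and safety assessment is narrowed rather than abandoned.

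Confidence in the mismatch is high, because it can be read directly from the two texts. The lateness of the change is an inference from one past-tense statement. How much the loss matters in practice depends on the YMRS scores and the reasons for stopping, which the documents cannot show. The change should be made, but it does not put the main efficacy analysis in doubt.

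**What to change.** In SAP section 2, restore the YMRS as a secondary outcome. In section 3.2, restore the protocol's ANCOVA of YMRS change, and add discontinuation by cause and by arm for all randomised patients. Use the four removal grounds in the protocol's Ethical and safety considerations as categories, plus other withdrawal.

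If the YMRS or the reasons for stopping were not collected, or if the removal was deliberate, record it as a deviation. State the date, the reason and whether it was decided before any unblinded data were seen, and limit the safety conclusion accordingly.

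The cost is two more tables. No new data collection is needed if the protocol's schedule was followed; if it was not, the cost is the deviation entry and a narrower safety statement.

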We do not anticipate any major risks related to the intervention. However, we acknowledge that potentially vulnerable people with mental illness will be participating in the trial. Some topics discussed or questions asked in the sessions/assessments may cause distress, and in such instances, appropriate support will be provided. We will map available mental health resources ensuring pathways to care. The research team has considerable clinical and research experience, including the management of difficult situations arising in research interventions and interviews. In case participant recruited to this study experience active suicidal ideation or subsequently identified as needing more intensive treatment will be appropriately referred for psychiatric evaluation and treatment. Patients will be removed from the study if they report suicidal attempt, became pregnant, developed a severe medical condition, or suffered from newly emerging side effects that they find intolerable and that could not be managed. Patients who will be removed from the study will receive antidepressant treatment as appropriate as part of clinical care. Research staff will be provided with regular supervision throughout the duration of the project. We already have study protocols in place that include details about how to manage difficult situations arising in research, safety and lone working arrangements. In the event of any study-related injury or adverse event, intervention and treatment will be available from medical staff. Any adverse events will be reported to the REB within the required timeframe.

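### The SAP drops cause-specific discontinuation and plans no by-arm table of suicidality or adverse events, so the safety aim rests on a symptom checklist, FIBSER and pooled dropout

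*Combined protocol and SAP*

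**What the plan says.** SAP section 1 sets the purpose: "The aim of this trial is to determine the efficacy and safety of MBC in patients with MDD". Its hypothesis on harms is narrower: the MBC arm is expected to do better on response and remission, "along with lower rates of dropout and side effect burden".

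SAP section 2 gives two harm measures. The first is a symptom list: "An additional checklist with six common side effects (dry mouth, diarrhea or constipation, dizziness or drowsiness, loss of appetite or nausea, headache, and excessive sweating"). The second is the FIBSER scale, which the section spells differently, and both are tied to treatment visits: "and the FISBER, will be used to measure side effects at each treatment visit".

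SAP section 3.2 lists what is compared between arms. The items that bear on safety are "discontinuation, response and remission rates, and side effects as appropriate". A separate sentence there deals with dropout: "Full intent-to-treat analyses will be carried out to determine all-cause discontinuation".

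The matching sentence in the protocol's Statistical analysis section covers discontinuation both from any cause and by specific cause. The SAP keeps only the first.

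The protocol's Ethical and safety considerations section says what happens to patients with serious events: "Patients will be removed from the study if they report suicidal attempt, became pregnant, developed a severe medical condition". New side effects that a patient cannot tolerate and that cannot be managed are a further ground for removal. Patients with active suicidal ideation are referred for psychiatric evaluation. On reporting: "Any adverse events will be reported to the REB within the required timeframe".

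**The concern.** The protocol acts on suicide attempts, active ideation and adverse events, but the SAP does not carry them into any labelled comparison. There are two separate gaps.

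- **Attempts and other safety removals.** The protocol's cause-specific analysis would have separated these from people who moved away or withdrew consent. The SAP leaves that analysis out without comment.
- **Ideation referrals, adverse events and serious adverse events.** No by-arm analysis of these is planned in either document.

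The gap matters because of the claim the trial hopes to make. It hypothesises a lower side-effect burden with MBC, and its introduction reports that the earlier Chinese trial it replicates had more treatment adjustments and higher antidepressant doses under MBC. If the SAP is followed as written, a favourable safety statement could rest on items such as dry mouth and headache while the distribution of the gravest events by arm stays unreported.

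**Working it through.** The plan states no figure for any safety comparison, so there is none to reproduce. The check is to trace each type of event through the two documents, then ask what a table could show at this sample size.

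**Step 1. Where each event would appear**

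| Event | Protocol action | Protocol analysis | SAP analysis |
|---|---|---|---|
| Suicide attempt | Removal | Any-cause and specific-cause discontinuation | Any-cause discontinuation only, unlabelled |
| Intolerable side effects leading to removal | Removal | As above, plus side-effect measures | Any-cause discontinuation, plus side-effect measures |
| Active suicidal ideation | Referral | None named | None named |
| Adverse or serious adverse event outside the checklist and FIBSER | Reported to the ethics board | None named, unless it causes removal | None named; unlabelled if it causes removal |

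**Step 2. Arm size.** Protocol, Sample size: 120 participants. Protocol, Randomization and masking: 1:1 allocation. So 120 / 2 = about 60 per arm.

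**Step 3. What pooling can hide (assumed counts).** Suppose there are 3 attempts with MBC and 0 with standard care, inside dropout totals of 15 and 15.

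- All-cause comparison: 15/60 against 15/60, chi-square p = 1.0. This needs 15 − 3 = 12 other dropouts with MBC against 15 with standard care, an offset chosen to make the point.
- Labelled comparison: 3/60 = 5.0% (exact 95% CI 1.0% to 13.9%) against 0/60 = 0% (upper limit 6.0%).

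**Step 4. What a labelled table can establish.** With no events in one arm and k in the other, the two-sided Fisher p at 60 per arm is 2 × C(60,k) / C(120,k).

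- k = 3: 2 × 34,220 / 280,840 = 0.24
- k = 5: 2 × 5,461,512 / 190,578,024 = 0.057
- k = 6: 2 × 50,063,860 / 3,652,745,460 = 0.027

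So at least 6 against 0 is needed for p < 0.05. With no events in an arm, the upper limit of the two-sided 95% interval is 1 − 0.025^(1/60) = 6.0%.

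**Step 5. Would the table be empty?** The documents give no event rate, so a range is assumed. The chance of at least one event among 120 is 1 − (1 − p)^120: 70% at p = 1%, 91% at 2% and 99.8% at 5%. Power of Fisher's test is low throughout: 5% for 1% against 5%, and 28% for 2% against 10%.

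**The case against.** Several points on the other side are sound.

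- **Attempts are not wholly outside the analysis.** A reader might infer that no planned analysis touches suicide attempts. The documents do not support that. An attempt forces removal, so it counts in the SAP's all-cause comparison, and the protocol's cause-specific analysis covered it by name of cause. For attempts, the defect is a discrepancy between SAP and protocol.
- **Data may not be held.** A reader might assume that these events are already recorded and need only be tabulated. The protocol gives rules for removal, referral and reporting, but names no instrument, schedule or case-report item for ideation or adverse events. SAP section 3.1 speaks of interim analyses in the past tense, which suggests that the SAP was written late, so what was not collected may be lost.
- **There is other oversight.** The protocol's Data management and monitoring section has a Data Safety and Monitoring Committee watching for ethical or safety reasons to stop. That is relevant, but no by-arm safety results are specified for it, and it does not replace a final comparison.
- **Nothing shows that MBC is more harmful.** The protocol expects no major risks from the intervention. Table 1 also directs continuing the dose, addressing side effects or switching drug, so it is not purely a dose-escalation scheme. No imbalance should be inferred.
- **The trial is small and described as exploratory.** By Step 4, even a labelled 3 against 0 would give p = 0.24.

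These points limit the claim and the promise of the fix. They leave the core in place: the stated aim includes safety, and the SAP would not report the gravest named events by arm.

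**Conclusion.** The point holds in a bounded form and should be corrected. The SAP restricts safety analysis to the checklist, FIBSER and discontinuation from any cause. It drops the cause-specific analysis that the protocol planned, and neither document plans a by-arm comparison of ideation referrals, adverse events or serious adverse events.

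The size cannot be taken from the documents, which give no event or dropout counts. The 3 against 0 and 15 against 15 figures are illustrations, and the 1% to 5% rates are assumptions. The conclusion about the missing analyses does not depend on them. The limits on precision depend only on about 60 patients per arm.

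**What to change.** 1. In SAP section 3.2, restore discontinuation by specific cause, by randomised arm, and reconcile it with the protocol's Statistical analysis section. Show suicide attempt and each other safety reason for removal as separate causes.
2. Add one descriptive table by randomised arm, from randomisation to week 24, of patients with at least one: suicide attempt; referral for active suicidal ideation; death or serious adverse event; adverse event reported to the ethics board. Give counts, proportions, risk differences and exact 95% confidence intervals.
3. Name the source of each row (removal, referral and ethics-board records, to the extent held) and its limits, including whether events after removal from the study could be known.
4. State that the safety conclusion rests on this table together with the checklist and FIBSER.

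The analysis cost is a change of SAP wording and one table. The effort of assembling the records is unknown, because the documents do not say how these events were captured; where a row cannot be filled reliably, the report should say so. The intervals will be wide, so the table should be labelled descriptive and should not be read as evidence of equal safety. No change to patient management is implied.
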